### Data management

Data from each participant in the preliminary study phase and/or the trial will be recorded in the study database by Asia Injury Prevention Foundation (AIPF) staff. Standard validation procedures will be implemented to ensure consistency, reliability and full compliance with Good Clinical Practice (GCP) [25] and other pertinent regulatory requirements. The database with CNC and compliance information will be under the custodianship of University of Medicine and Pharmacy (UMP). NICTU’s standard procedures for data backup, storage and security will be strictly followed for data entered into the trial management software. Access to these data will be restricted to authorised personnel.

### Statistical analyses

All outcomes for trial participants will be analysed in accordance with the intention-to-treat (ITT) principle. Baseline characteristics will be summarised using means and standard deviations, medians and interquartile ranges, or numbers and percentages, as appropriate. The primary outcome (number of CNC events per 1000 km driven) will be analysed using generalised linear mixed models, reporting mean differences and adjusting for cluster, secular and time effects. For example, secular trend adjustments will take into consideration national and regional driving safety campaigns and calendar time. Seasonal factors (amount of daylight, inclement weather, etc.) are likely to play a role in the number and severity of CNC events. Analysis of secondary outcomes will be done in a similar fashion. Risk differences for binary outcomes and mean differences for continuous outcomes, all adjusting for cluster, secular and time effects, will be reported.

Sensitivity analyses will be conducted to examine the intervention effects, adjusting for additional pre-specified potential confounders including age (years as a continuous variable), DDDI risk profile [24] (total score as a continuous variable) and residence (rural/urban as a binary variable).

Missing data will likely result when participants withdraw from the study or do not complete the full follow-up. Multiple imputations of missing data when assessing secondary outcomes will involve creating 20 copies of the data and imputing missing values by chained equations before averaging the datasets [26].

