#### Secondary outcomes

Secondary outcomes include self-reported visual function (driving-adapted Visual Function Questionnare-25 [VFQ-25]) [22] administered at baseline and 1 month after receiving spectacles; self-reported crashes and injuries reported every 2 weeks by questionnaire (Crash and Injury Self-Report Questionnaire [CI SRQ]); self-reported crashes (compared with DAS-recorded crashes); and total delivery cost per CNC event avoided in the intervention condition (as an indicator of cost-effectiveness).

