### Sample size

Unpublished data from Dynamic Vision, an organisation currently collecting CNC events from motorcycle drivers in Vietnam, were used to inform the power calculation. Results showed an estimated mean event rate of 1.67 CNC events per 1000 km driven (standard deviation [SD] = 0.556). For a postulated, clinically meaningful 10% reduction in CNC events, a stepped-wedge cohort design comprising six sequences of seven myopic participants per cluster (a 28% prevalence, below the 40% figure observed during pilot testing with the WHOeyes app), a coefficient of variation of cluster sizes of 3, and five clusters per sequence with Individual Auto Correlation (IAC) of zero, confer 90% power (mean difference = 0.167, SD = 0.556; intraclass correlation [ICC] = 0.02 [0.01–0.05]) [23]. This would be achieved by collecting DAS data from 175 students over the course of 72 weeks. To achieve this, 5200 students will be invited to self-assess their vision using WHOeyes. Pilot data indicate that approximately 12%, or 625 students, will fail that assessment and be eligible to join the preliminary phase of the study, with placement of DAS units on their motorcycles. An estimated 250 (40% of those failing the WHOeyes self-assessment) will have eligible, uncorrected/under-corrected myopia detected on their subsequent eye examination by an optometrist. They will then be assigned to the intervention condition and given free spectacles. With a 30% dropout rate, this will result in complete datasets for 175 participants over the course of the trial.

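### For secondary outcomes, the protocol combines 20 imputations by averaging the datasets; followed as written, this makes standard errors too small and leaves imputed binary outcomes as fractions

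*Protocol article*

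**What the plan says.** The Statistical analyses section of the protocol article expects incomplete data: "Missing data will likely result when participants withdraw from the study or do not complete the full follow-up". It confines imputation to one set of analyses: "Multiple imputations of missing data when assessing secondary outcomes". It then fixes the method, which "will involve creating 20 copies of the data and imputing missing values by chained equations before averaging the datasets", and cites a methods reference.

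The same section says what these analyses must deliver: "Risk differences for binary outcomes and mean differences for continuous outcomes, all adjusting for cluster, secular and time effects, will be reported".

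Under Secondary outcomes, the visual function questionnaire (VFQ-25) is "administered at baseline and 1 month after receiving spectacles", and crashes and injuries are self-reported every 2 weeks.

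The Sample size section gives the only figure for loss: "With a 30% dropout rate, this will result in complete datasets for 175 participants over the course of the trial".

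Nowhere does the article say that each imputed dataset is analysed separately, that estimates are pooled, or how variances are combined.

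**The concern.** Multiple imputation yields valid standard errors because the analysis is repeated in each completed dataset and the spread of the estimates is added to the average within-dataset variance. If the datasets themselves are averaged, three things happen:

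- Each imputed value becomes the mean of 20 draws, close to its predicted mean, so its residual variation largely disappears.
- The between-imputation variance is lost, because only one dataset is left.
- The imputed values count as observed data.

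The result is close to single mean imputation. Confidence intervals for VFQ-25 and for self-reported crashes and injuries would be too narrow and their p-values too small. For a yes/no outcome, the averaged values are no longer 0 or 1.

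This is not a detail left to the analysis plan. The article does state a combination step, and that step is wrong as worded. An analysis plan that followed it would inherit the error, and one that pooled correctly would contradict the published protocol.

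**Working it through.** **The plan's own figures.** From the Sample size section: 5200 × 0.12 = 624 (stated as 625); 625 × 0.40 = 250; 250 × (1 − 0.30) = 175. The funnel reproduces. Any calculation should therefore start from n = 250 with up to 30% missing, since 175 is already net of dropout. The article gives no numerical result for the imputation itself.

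**Analytic check.** Let f be the missing fraction and m = 20, with no useful predictors of the missing values.

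- The variance in the averaged dataset is about σ²[(1 − f) + f/m], and the analysis divides it by n.
- The information actually available gives a variance of about σ²/[(1 − f)n].
- The ratio of reported to true standard error is therefore √[(1 − f) + f/m] × √(1 − f).
- A nominal 5% test then uses an effective critical value of 1.96 × ratio.

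| Missing | SE ratio | Effective critical value | Type I error |
|---|---|---|---|
| 10% (assumed) | √0.905 × √0.90 = 0.90 | 1.77 | about 8% |
| 15% (assumed) | √0.8575 × √0.85 = 0.85 | 1.67 | about 9% |
| 30% (Sample size section) | √0.715 × √0.70 = 0.71 | 1.39 | about 17% |

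**Simulation.** Settings: n = 250, m = 20 proper imputations, missing completely at random, no clustering, 3,000 replicates per scenario. Each run was analysed twice: once on the averaged dataset, and once by Rubin's rules with total variance T = U + (1 + 1/m)B, where U is the mean within-imputation variance and B the between-imputation variance.

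Results at 30% missing:

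| Comparison | SE ratio, averaged to Rubin | Coverage of nominal 95% interval, averaged |
|---|---|---|
| Paired before/after, correlation 0 | 0.84 | 90.8% |
| Paired, correlation 0.3 | 0.79 | 87.1% |
| Paired, correlation 0.5 | 0.77 | 85.7% |
| Paired, correlation 0.7 | 0.74 | 85.4% |
| Two conditions, continuous | 0.70 | 82.4% |
| Two conditions, binary, 20% risk | 0.71 | 82.9% |

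- Type I error is 100% minus coverage: 9.2% to 17.6% over the table, of which 9.2% to 14.6% in the paired rows. A second paired simulation at n = 250 gave about 12–17%.
- Rubin's rules gave 94.3–95.6% coverage in these scenarios.
- At an assumed 10% missing, averaging gave an SE ratio of 0.90–0.95 and coverage of 92.1–93.7%, a type I error of 6.3–7.9%. The second paired simulation gave 6–8%.
- In the paired scenarios the point estimate was identical under the two methods, as it must be for a linear mean difference.
- In the binary scenario about 98% of the averaged imputed values lay strictly between 0 and 1.

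The correlations, the 20% risk, the 10% and 15% missing fractions, the missingness mechanism and the absence of clustering are assumptions. The standard error was too small in every scenario.

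**The case against.** The strongest objection is that the phrase is shorthand. The sentence names multiple imputation, 20 copies and chained equations, and cites a methods reference that is not available here. It never says outright that a single averaged dataset is then analysed. The section also promises risk differences for binary outcomes, which the literal procedure could hardly deliver, and standard software pools correctly by default. A slip of wording is therefore plausible. This bears on how likely the harm is, but it does not rescue the sentence. What it says is averaged is the datasets, nothing else in the article corrects it, and even the charitable reading leaves the standard error without a rule.

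The other objections concern size and scope, and they stand:

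- A reader might infer that 30% of every secondary outcome will be missing. The documents do not support that. The 30% is the share of participants without complete datasets over the trial. VFQ-25 is taken 1 month after spectacles, so dropout after that point costs it nothing. Crash reports come every 2 weeks, so those who leave still contribute earlier records. If dropout were spread evenly over follow-up (an assumption), about 15% of crash records would be missing.
- A reader might take 175 participants and remove a further 30%. That applies dropout twice.
- A reader might quote only the two-condition results, near 18%. Participants in this trial supply both control and intervention data, and the paired rows are milder.
- A reader might infer that the trial's main result is at risk. It is not, because imputation is stated for secondary outcomes only.
- A reader might want the contents of the imputation model listed as well. The article states nothing wrong about them, and a protocol commonly leaves them to the analysis plan.

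**Conclusion.** The stated combination step is wrong as worded and should be corrected, as a matter for the secondary outcomes only. If it were followed literally, type I error would be roughly 6–9% at an assumed 10–15% missing and roughly 9–18% at 30% missing, the last being an upper-end case. Where a figure falls within these ranges depends on the missing fraction, the design of the comparison and how well the imputation model predicts the missing values. The harm is to standard errors, confidence intervals and p-values and, for binary outcomes, to the ability to fit the model at all. The documents do not show that the investigators intend to analyse one averaged dataset, so these figures are conditional on the literal reading.

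**What to change.** Replace the closing words of the imputation sentence with: *fit the analysis model in each of the 20 imputed datasets and combine the treatment estimates and variances using Rubin's rules.*

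The cost is one sentence. Standard software does this by default, and no change to design, data collection or sample size is needed. Any analysis plan should carry the same wording, so that it neither repeats the published sentence nor appears to depart from it without explanation.

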### Trial monitoring

The trial will be independently monitored by a Data Monitoring and Ethics Committee (DMEC), with the remit to protect and serve study participants, especially regarding safety, and to assist and advise the chief investigator to protect the validity and credibility of the trial. No interim analyses of the trial outcomes are planned.

### Protocol compliance

A protocol deviation is defined as a failure to adhere to the protocol, such as delivering an incorrect intervention or errors in applying eligibility criteria. Major protocol deviations constitute instances where enrolled participants have not provided informed consent or deliberately provide incorrect data. Other protocol deviations include situations where participants are incorrectly randomised, or where participants in the intervention condition have not receive the prescribed spectacles.

### Participant confidentiality

The chief investigator and local principal investigator are responsible for assuring participant privacy. All participant information and records in the study will be pseudo-anonymised with an identification code. Electronic and paper-based data that could reveal a participant’s identity will be securely stored on a server with access limited to designated study personnel, or in locked filing cabinets at UMP until data collection is completed. Anonymised data will be retained for 10 years in accordance with the funder’s requirements (https://www.ukri.org/wp-content/uploads/2020/10/UKRI-020920-ConcordatonOpenResearchData.pdf) and then treated as confidential waste and destroyed.

## Discussion

Road traffic crashes are the leading cause of mortality among people aged 5–29 years, and 90% of this burden falls on LMICs [1]. Poor vision due to uncorrected refractive error in Vietnam and Southeast Asia, especially among young people [7, 11, 12], has been shown in a recent meta-analysis to increase the risk of road crashes by 46% [15]. Despite evidence of the link between good vision and road safety, there are few studies on interventions to reduce crash risk by treating vision disorders such as myopia [17–19]. The recent meta-analysis and review by Piyasena et al. found no randomised trials on vision care and traffic safety in LMICs [16]. The STABLE trial will help to fill this knowledge gap by examining the effects of spectacles to correct myopia to reduce crashes among university students in Vietnam. It will be the first randomised trial of vision interventions and driving safety in a LMIC and a successful trial outcome will help to inform strategies to reduce traffic crashes in the future through wide dissemination and engagement with policy makers.

### Trial status

This paper is based on version 4.2 of the STABLE protocol (dated 15 May 2024). Important changes to the protocol will be communicated to the relevant ethics committees and trial registries as needed. Recruitment to STABLE is expected to start and be completed (given the stepped-wedge design which requires all participants to be included at the outset) in the fourth quarter of 2024.

## Data Availability

Following publication of the results for the primary and secondary outcomes, there may be scope for supplementary analyses by third parties on the data collected. In such cases, written formal requests to access the data must be sent to the chief investigator through the NICTU for discussion with the sponsor. The study will comply with good practice principles for sharing individual participant data from publicly funded clinical trials [27, 28]. Data sharing will be undertaken in accordance with the required regulatory requirements. In the event of publications arising from these analyses, those responsible will provide the chief investigator with a copy of the intended manuscript for approval before submission and acknowledge the source of the data they use. No identifying images or other personal or clinical details of participants are presented here or will be presented in reports of the trial results. The participant information materials and informed consent form are available from the corresponding author on request.

## Abbreviations

LMICs: Low- and middle-income countries
STABLE: Slashing Two-wheeled Accidents by Leveraging Eyecare
DAS: Data Acquisition Systems
CNC: Crash-near crash
WHO: World Health Organisation
SW-CRT: Stepped-wedge, cluster randomised trial
VFQ-25: Visual Function Questionnare-25
CI SRQ: Crash and Injury Self-Report Questionnaire
IAC: Individual Auto Correlation
ICC: Intraclass correlation
QUB: Queen’s University Belfast
NICTU: Northern Ireland Clinical Trials Unit
LVPEI CTU: LV Prasad Eye Institute Clinical Trials Unit
AE: Adverse events
SAEs: Serious adverse events
AIPF: Asia Injury Prevention Foundation
GCP: Good Clinical Practice
DDDI: Dula Dangerous Driving Index
ITT: Intention-to-treat
UMP: University of Medicine and Pharmacy
DMEC: Data Monitoring and Ethics Committee
ICH: International Conference on Harmonisation
ENGINE: Eyecare Nurtures Good-health, Innovation, driviNg-safety and Education
